### Patient discontinuation or protocol violation

Cohort patients meeting any of the following criteria will be classified as **withdrawn**

- **Withdrawal of consent:**

Any patient may withdraw consent at any time, without prejudice for further follow-up or treatment in the study site.

- **Failure to complete the treatment due to either:**
- Failure to attend the scheduled visits during the 10-day treatment;
- Serious adverse events necessitating termination of the treatment before the full course (10 days) of the treatment is completed;

A patient who vomits twice the study medications will be withdrawn from the study and given the rescue treatment.

A patient can be discontinued from the study if the investigator decides that a patient should be withdrawn for safety reasons due to serious adverse events (signs of hemolytic anemia (yellow conjonctives/dark urine) or Grade 3 to 4 of the WHO classification for adverse events). In this case, information concerning the adverse event and symptomatic treatment given must be recorded on the patient follow-up form (Annex 7).

- **Voluntary protocol violation (28-day follow-up)**

Self- or third party administration of antimalarial (or antibiotics with antimalarial activity such as tetracycline, amoxicilline).

- **Involuntary protocol violation (during the 28-day follow-up)**
- Occurrence of concomitant disease that would interfere with a clear classification of the treatment outcome;
- Detection of another malaria species during the follow-up;
- Erroneous inclusion of a patient who do not meet the inclusion criteria;
- Misclassification of a patient due to a laboratory error (parasitaemia) leading to the administration of the rescue treatment;

**Patients who are withdrawn will be followed up until day 28 and continue the 2-year monthly follow-up.** However, no treatment outcome will be assigned to these patients during the 28-day follow-up. The reason for discontinuation or protocol violation will always be recorded on the follow-up forms (Annex 7 or Annex 8, accordingly).

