### Loss to follow-up

Loss to follow up occurs when, despite all reasonable effort, an enrolled patient that does not attend the scheduled visits cannot be found. No treatment outcome will be assigned to these patients during the 28-day follow-up. These patients will be classified as lost to follow-up. Patients who are lost to follow-up, but who subsequently come back to the study site before the end of the 28-day follow-up (or the end of the 2-year follow-up), will not be turned away and will also be encouraged as much as possible to return into the follow-up. The reason and location (geographical) of the absence must be written in the follow-up forms Annex 7 or Annex8, accordingly). These patients will be classified as “temporarily lost”.

Every effort must be taken to trace the patients for their follow-up visits with the help of the HHW (and community members) during the entire follow-up period.

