### Sample size calculation

Two different sample sizes were calculated: one for the estimation of *P.vivax* failure rate for chloroquine (28-day follow-up) and for Primaquine (2-year follow-up) in a cohort of *P.vivax* patients initially treated with the current radical cure regimen, and the second for the population survey on *P.vivax* prevalence (in a random sample of the study population).

- ***P.vivax population survey***

A total2,100 individuals at risk of malaria were estimated in the 4 study communes (census February 2009). According to the provincial malaria station (PMS) data on surveys carried out in April-May, the overall parasite rate was around 16% (ranging from 5 to 39% across hamlets) and the prevalence of *P.vivax* at 9%. In order to detect a minimal prevalence of 9% with 3% precision and at 5% significance level, a total of 300 individuals is needed for the survey (“CSample” command/EpiInfo6). After “finite population correction” and adding 10% security margin, a final sample size of 300 individuals would be sufficient. Since there are a total of about 370 households and in order to simplify sampling procedures, one individual in each house visited for the screening will be randomly selected to participate in the survey. This will be done by randomly choosing from the census file. The selected individual will be asked oral informed consent before starting in-depth interview.

- ***P.vivax cohort***

Between 2003 and 2007, *P. vivax* late parasitological failure to CQ was monitored in several Central Vietnam provinces and ranged from 0% to 5.7% (13). Therefore, to detect a failure rate as low as 5% with a 3% precision at 5% significance level, a minimum of 185 individuals are needed (“CSample” command/EpiInfo6). Assuming a maximum drop out rate of 10% during the first 28 days, a total of 204 cases will be necessary. For the estimation of a similar PQ failure rate after 2 years of follow-up, a total of 230 patients should be included with a maximum of 20% drop out during the 2-year follow-up.

By including 250 vivax patients in the cohort, and assuming a maximum drop out rate of 20% during the 2-year follow-up, we can expect to get a final database of 200 patients with a complete follow-up (i.e. 31 successive sampling results) for the modelling of *P.vivax* new infections/relapses.

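### Lost and withdrawn patients get no day-28 treatment outcome, so valid follow-up goes unused and it is unclear whether a failure already met still counts

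*Protocol*

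**What the plan says.** Protocol section 3.2.5 (Study endpoints) names two primary endpoints: treatment failure at day 28, and the incidence of recurrent *P. vivax* infection after day 28. Treatment failure is the sum of early and late failures, and no enrolled patient is excluded from that definition.

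Sections 3.2.2 and 3.2.3 then restrict who gets an outcome:

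- **Lost patients.** Loss means that "an enrolled patient that does not attend the scheduled visits cannot be found". The rule is "No treatment outcome will be assigned to these patients during the 28-day follow-up".
- **Withdrawn patients.** The reasons include consent withdrawal, missed visits during the 10-day treatment, use of other antimalarials, interfering disease, another malaria species, erroneous inclusion and laboratory error. They also include "Serious adverse events necessitating termination of the treatment before the full course (10 days) of the treatment is completed" and "A patient who vomits twice the study medications will be withdrawn from the study and given the rescue treatment". On follow-up the section says "Patients who are withdrawn will be followed up until day 28 and continue the 2-year monthly follow-up". The next sentence is "However, no treatment outcome will be assigned to these patients during the 28-day follow-up".

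Table 2 schedules blood films on days 0 to 3, 7, 14, 21 and 28. Section 3.2.6 allows for these losses only through sample size: "Assuming a maximum drop out rate of 10% during the first 28 days". Section 3.4 limits the cohort analysis to samples with *P. vivax* mono-infection at inclusion.

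**The concern.** Three things follow from reading the rule as written.

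1. **Selection after enrolment.** Vomiting the drugs and missing treatment visits bear on drug exposure. Self-treatment may be a response to persisting symptoms, and the Background says that self-treatment is common and adherence usually low. If such patients would fail more often, a failure rate based on the remainder is too low.
2. **Usable follow-up is set aside.** Section 3.2.6 describes the 28-day phase as estimating chloroquine failure, and chloroquine ends on day 2. A patient who completed chloroquine but misses a primaquine visit on day 8 has no outcome, whatever the slides before that day showed.
3. **No order of precedence.** A patient may meet an early-failure criterion on day 3, remain in follow-up as section 3.2.4 requires, and take another antimalarial on day 15. Section 3.2.5 makes this patient a failure; section 3.2.3 assigns no outcome. Two analysts could classify the patient differently.

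**Working it through.** **Inputs from section 3.2.6.** Failure rate 5%, precision 3 points, significance level 5%, minimum 185 patients, 10% drop-out to day 28 giving 204, planned cohort 250.

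**The plan's own figure.** n0 = 1.96² × 0.05 × 0.95 / 0.03² = 202.7. With a finite population correction at N = 2,100, n = 202.7 / (1 + 202.7/2,100) = 184.9, so 185. Section 3.2.6 gives that population for the survey; its use for the cohort is inferred from the match. For 10% drop-out, 185/0.9 = 206 and 185 × 1.10 = 204, the stated number. Inflating the sample in this way suggests a failure rate calculated among patients with an outcome.

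**Precision is not the problem.** With 225 evaluable patients, the half-width at 5% is 1.96 × √(0.05 × 0.95/225) = 2.8 points. Inflation for drop-out protects the width of the interval, not its position.

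**Illustration.** Assume 250 enrolled, 25 (10%) without an outcome and 11 failures among the other 225.

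- Evaluable-only: 11/225 = 4.9%, exact 95% CI 2.5% to 8.6%.
- Unassigned fail at 10%: (11 + 2.5)/250 = 5.4%.
- Unassigned fail at 20%: (11 + 5)/250 = 6.4%.
- Extreme bounds: 11/250 = 4.4% if none fail; (11 + 25)/250 = 14.4% if all fail.

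The failure rates in the unassigned are assumptions, because the Protocol gives none. The unassigned share is also unknown, so it is varied here:

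| Unassigned of 250 | Failures/evaluable | Evaluable-only | Unassigned at 10% | Unassigned at 20% | Bounds |
|---|---|---|---|---|---|
| 12 | 12/238 | 5.0% | 5.3% | 5.8% | 4.8 to 9.6% |
| 25 | 11/225 | 4.9% | 5.4% | 6.4% | 4.4 to 14.4% |
| 50 | 10/200 | 5.0% | 6.0% | 8.0% | 4.0 to 24.0% |

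**Shift of 3 points, from 5% to 8%.** With 10% unassigned, 0.90 × 0.05 + 0.10 × q = 0.08 gives q = 0.35. With 20% unassigned, 0.80 × 0.05 + 0.20 × q = 0.08 gives q = 0.20.

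**What Kaplan-Meier does by itself.** With the same 11 failures, the estimate is 11/225 = 4.9% if all 25 are censored before the first failure and 11/250 = 4.4% if all are censored after the last. Censoring alone therefore moves the figure by at most 0.5 points, and downwards. Counting failures met before withdrawal moves it up: one such failure gives 12/250 = 4.8% instead of 4.4% when the other patients are censored late.

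**The case against.** The strongest reply is that sections 3.2.2 and 3.2.3 state a classification rule, not an estimator. Section 3.5 names no denominator or interval for day-28 failure, and a patient without an assigned outcome could still be censored in a time-to-event analysis. A statistical analysis plan may say so. This stands in part: a reader might infer that the Protocol fixes a complete-case proportion, and no section says that. But a later plan that counted a failure in a withdrawn patient would have to depart from the Protocol's wording.

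A second reply is that efficacy under directly observed treatment is a coherent target, and that setting aside patients who vomited the drugs or took other antimalarials fits it. That also stands in part. It does not explain setting aside patients who completed chloroquine, nor does it settle precedence.

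Several stronger readings are not supported:

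- *All these patients have slides to day 28.* Only withdrawn patients remain under follow-up, and those who withdraw consent may have none. Lost patients have slides up to loss; those who return are classed separately as temporarily lost.
- *Up to 10% of the cohort is discarded.* The 10% is a planning assumption for drop-out, neither a cap nor a count. The text does not say whether it includes protocol violations.
- *Primary efficacy as a whole is affected.* The rule is confined to the 28-day phase; withdrawn patients continue into the 2-year follow-up.
- *All the reasons are outcome-related.* Erroneous inclusion and another malaria species are not clearly so.
- *Positive slides are thrown away.* Nothing says that a later violation cancels a failure already met. The text is silent, which is the ambiguity.

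**Conclusion.** The point holds for the day-28 treatment-failure endpoint. The Protocol assigns no outcome to patients whom it continues to observe, or observed up to loss, for reasons of which some are plausibly linked to exposure or outcome. It does not reconcile this with an endpoint definition that excludes nobody.

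The likely bias is modest. With 10% unassigned, plausible excess failure moves 4.9% to 5.4% or 6.4%, inside the interval of 2.5% to 8.6%. The 14.4% bound needs every unassigned patient to fail and marks an extreme only; section 3.2.6 cites late parasitological failure of 0% to 5.7% in earlier monitoring. A reader might infer that the reported failure rate will be seriously too low. The figures do not show that, unless the unassigned share or their failure rate is well above the planning values. The change is worth making because the ambiguity is real and removing it is cheap. The sizes rest on the assumed 250 enrolled, 11 failures, unassigned share and failure rates among the unassigned.

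**What to change.** Amend sections 3.2.2 and 3.2.3 as follows:

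1. Any early or late treatment failure met before loss or withdrawal counts as a failure.
2. All other lost or withdrawn patients with confirmed *P. vivax* mono-infection at inclusion (section 3.4) are censored in a Kaplan-Meier estimate of day-28 failure, at the date of loss, violating drug or rescue treatment. Erroneous inclusions stay out. State the date to use where none of these events occurred, such as a missed treatment visit; the date of withdrawal agrees with item 1.
3. The evaluable-only proportion is kept as a secondary figure.
4. A sensitivity range is reported for patients without a day-28 outcome, because Kaplan-Meier alone does not remove bias from informative censoring. Slides taken after withdrawal can inform it where they exist.

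The cost is a few sentences and slightly more analysis. Visits, slide results and withdrawal reasons are already recorded, and no treatment or visit changes. The drawback is that the main estimate assumes non-informative censoring, which is why item 4 must accompany it.

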### Rescue treatment

- With any sign of severe malaria, the patient should be administered parenteral antimalaria treatment with either quinine or artesunate (IV) following national guidelines;
- If a patient meets one of the criteria for therapeutic failure (ETF, LTF), he/she will receive Arterakin for 3 days following the national guideline. However, this patient will remain in the 2-year monthly follow-up, and thus should be re-assessed clinically and biologically at Day 28 (following D28 procedures mentioned in Annex7), and then enter the monthly follow-up.
- If the patient is re-infected with *P.falciparum* (mono- or mixed infection) he/she will receive the rescue treatment with Arterakin for 3 days following the national guideline.

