### Cohort recruitment

Vivax infected patients will be recruited during the initial screening/survey and/or during one year of the passive case detection (PCD) continued in each study village during the whole cohort follow-up.

Initially, the recruitment period was foreseen from April 2009 to April 2010. Since only 117 *P.vivax* patients could be recruited by February 2010, it was decided to extend the recruitment until December 2010 in order to reach the target number of 250 patients included.

*Inclusion criteria*

- Age ≥ 3years
- *P.vivax* mono-infection (asexual stages);
- Resident in the study villages;
- Written informed consent (parent/guardian for minors);

*Exclusion criteria*

- General danger signs with severe or complicated malaria according to WHO definitions (Annex B to this protocol);
- Pregnancy (rapid test positive or pregnancy clinically confirmed) or breastfeeding;
- Known G6PD deficiency (or history of “black urine” after previous primaquine treatment), or any history of side effects to the study drug;
- Documented radical cure with Primaquine (10 days at 0.5mg/kg) within one month prior to inclusion;
- Underlying chronic diseases (TB, lupus, diabetes, rheumatoid arthritis, etc);
- Concomitant infectious disease requiring antibiotic treatment;
- Severe malnutrition;
- Patients with neuro-psychiatric disorders or previous history (epilepsy, dementia, ..)

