***Treatment of patients in the cohort***

The new treatment guideline for the radical cure of *P.vivax* (2007) consists of 25mg/kg Chloroquine (CQ) over 3 days, together with Primaquine (PQ), 0.5mg/kg daily for 10 days, under the direct supervision of the study team (Table 1). Patients will be observed during one hour: in case of vomiting within the first 30 minutes, a full dose will be re-administered, only half dose if vomiting occurs between 30 minutes and 1 hour. The total number of tablets of each drug administered (+/- re-administrated dose if vomiting) will be recorded on the patient’s follow-up form (Annex7)

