**Table 2. Patients’ follow-up schedule during the first 28 days**

|  | **D0** | **D1** | **D2** | **D3** | **D4** | **D5** | **D6** | **D7** | **D8** | **D9** | **D14** | **D21** | **D28** | **Dx** | **M*** | **Mx** |
| --- | --- | --- | --- | --- | --- | --- | --- | --- | --- | --- | --- | --- | --- | --- | --- | --- |
| **PROCEDURES** |  |  |  |  |  |  |  |  |  |  |  |  |  |  |  |  |
| Clinical examination | **X** | **X** | **X** | **X** | **X** | **X** | **X** | **X** | **X** | **X** | **X** | **X** | **X** | **X** | **X** | **X** |
| Assess adverse event | **X** | **X** | **X** | **X** | **X** | **X** | **X** | **X** | **X** | **X** | **X** | **X** | **X** | **X** |  |  |
| Body temperature | **X** | **X** | **X** | **X** | **X** | **X** | **X** | **X** | **X** | **X** | **X** | **X** | **X** | **X** | **X** | **X** |
| Thick+thin film | **X** | **X** | **X** | **X** |  |  |  | **X** |  |  | **X** | **X** | **X** | **X** | **X** | **X** |
| Filter paper 2 spots  (ELISA & PCR) | **X** |  | **X** | **X** |  |  |  | **X** |  |  | **X** | **X** | **X** | **X** | **X** | **X** |
| Hemoglobin | **X** |  |  |  |  |  |  |  |  |  | **X** |  | **X** |  |  |  |
| Filter paper CQ  (100µl capillary) | **X** |  |  |  |  |  |  | **X** |  |  |  |  | **X** | **X** |  |  |
| Direct observation of treatment | **X** | **X** | **X** | **X** | **X** | **X** | **X** | **X** | **X** | **X** |  |  |  |  |  |  |

**Dx**: Any other day if the patient feels febrile or unwell

**M***: monthly visits by HHW from 2nd to 24th month

**Mx:** unscheduled monthly visit if patient feels sick

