***2-year monthly follow-up***

After completion of the 28-day follow up, patients will be visited monthly at home by a health staff from the study team. Each patient will be interviewed on malaria signs/treatment since the last visit, examined clinically (body temperature) and a blood sample (slide +filter paper) will be taken. All information will be recorded on a pre-coded standardised questionnaire (monthly follow-up form). In case a patient presents with a recurrent *P.vivax* parasitemia s/he will be treated with CQ alone for 3 days. In case of persistent *P.vivax* gametocytemia, the patient can be treated with a single dose of Primaquine (0.75mg/kg). *P.falciparum* mono- or mixed infections will be treated with Arterakine according to the national guidelines. Blood slides will be stained and read within 48h at Tra leng CHC and stored as well as filter papers in a dry, cool place.

If the patient is not available on the day of the scheduled visit, it is the responsibility of the HHW to trace him/her back before the next scheduled visit. If a patient cannot be traced for a whole month, the HHW has to report it (together with the reason of absence) on the monthly follow-up form. Cohort patients will be asked to consult their HHW (or the CHC) for any symptom appearing between the monthly scheduled visits, for clinical and biological examination by the study team.

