**ANNEX C. DRUG INTERACTIONS**

**DRUGS TO BE AVOIDED DURING PRIMAQUINE TREATMENT (interactions)**

- **DAPSONE:** leprosy, skin infections (Dapsone, DDS)
- **SULFONAMIDES:** antibiotic for bronchitis, urinary infections, diarrheas (Bactrim, Cotrim, Sulfatrim,…)
- **SULFOXONE:** sulfonamide for leprosy, dermatitis herpetiformis (Aldapsone, DDF, Diazone)
- **METHYLDOPA**: anti-hypertensive (Aldochlor, Aldoril)
- **FURAZOLIDONE:** infectious diarrhea and enteritis (Furoxone)
- **NITROFURANTOINE:** urinary tract infections (Furadantin)
- **QUINACRINE:** anti-malaria, antibiotic for Giardiasis (Atabrine)
- **QUINIDINE:** anti-arythmic (Cardioquin, Quinora , Quinidine SR …)
- **QUININE**: antimalarial (Quinine sulfate, Quinimax, etc…)
- **VITAMINE K:** prevention of bleeding in newborns (Phytonadione)

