**ANTIBIOTICS WITH ANTIMALARIAL EFFECT (Avoid during 28-day follow-up)**

- **Doxycycline**
- **Erythromycine**
- **Azythromycine**
- **Trimethoprim**
- **Clindamycine**
- **Rifampicin**
- **Pentamidine**

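### Section 3.2.4 allows quinine for severe malaria with no condition on primaquine, while Annex C says to avoid quinine during primaquine treatment

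*Protocol*

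**What the plan says.** Section 3.2.4 (Rescue treatment) opens with the rule for severe malaria: "With any sign of severe malaria, the patient should be administered parenteral antimalaria treatment with either quinine or artesunate (IV) following national guidelines". The two drugs are alternatives. No order of preference is given, and the rule does not ask whether the patient is taking primaquine.

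Annex C (Drug interactions) has a list headed "DRUGS TO BE AVOIDED DURING PRIMAQUINE TREATMENT (interactions". Among its ten entries is quinine, described as "antimalarial (Quinine sulfate, Quinimax" and similar products. The entry carries no exception for rescue. Artesunate is not on the list.

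The cohort regimen in section 3.3.3 includes "Primaquine (PQ), 0.5mg/kg daily for 10 days", given under direct supervision. Patients with severe disease are kept out at enrolment by the exclusion criterion "General danger signs with severe or complicated malaria according to WHO definitions (Annex B to this protocol".

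**The concern.** The rescue rule permits, without qualification, a drug that an annex of the same protocol says to avoid while the patient is on primaquine. A nurse or doctor facing a patient who deteriorates during the ten-day course would look to section 3.2.4, and nothing there signals that one of the two named drugs is on the avoid-list.

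What is at stake is patient safety in a rare situation and the internal consistency of the protocol. It is not the analysis. Section 3.2.5 counts danger signs with parasitaemia as treatment failure whichever rescue drug is given.

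**Working it through.** The plan states no figure to reproduce. The check sets the texts side by side and counts days.

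**1. Days on which primaquine is given.** The Day 0 instructions and the Day 1-9 instructions in section 3.3.3, and the directly observed treatment row of Table 2, all put primaquine on Day 0 through Day 9. That is 9 - 0 + 1 = 10 days.

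**2. Days on which the protocol foresees danger signs.** Section 3.2.5 counts danger signs with parasitaemia as follows:
- as early treatment failure on Days 0 to 3, of which 4 days fall in the primaquine course;
- as late clinical failure on any day after Day 3, of which Days 4 to 9, or 6 days, fall in the primaquine course.

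4 + 6 = 10, so every primaquine day is a day on which the rescue rule could be triggered. This is a count of calendar days, not a measure of risk.

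**3. The rescue options against the Annex C list.**

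| Rescue option in section 3.2.4 | On the Annex C primaquine list? |
| --- | --- |
| Parenteral quinine (severe malaria) | Yes, with no rescue exception |
| IV artesunate (severe malaria) | No |
| Arterakin for 3 days (other failures, *P. falciparum*) | Neither of its components, artesunate and piperaquine, is listed |

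Of the rescue drugs that section 3.2.4 names, only quinine conflicts with the list.

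**4. Whether another instruction removes the overlap.** Section 3.2.4 does not say that primaquine stops when parenteral rescue begins. Section 3.2.3 foresees ending treatment early for serious adverse events, but does not link this to the choice of rescue drug. The text therefore leaves open the use of quinine in a patient still on primaquine.

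**5. Effect on the endpoints.** A patient with danger signs and parasitaemia has met the failure definition before any rescue drug is chosen. Section 3.2.4 keeps patients who fail in the two-year follow-up. Neither primary endpoint is defined by the rescue drug, and no sample-size input involves it.

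**The case against.** The strongest reply is that the two texts do not contradict each other. Section 3.2.4 permits quinine but never requires it, and artesunate satisfies both texts. That stands, and it is why the point is minor. What remains is an unranked option that conflicts with the protocol's own list when a compliant option is named in the same sentence.

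A second reply is that the choice is subject to national guidelines, which may rank the drugs or say when to stop primaquine. They may, but the protocol does not show their content, and section 3.2.4 presents both drugs as acceptable under them.

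A third reply is that Annex C reads as advice on concomitant medication, gives no mechanism or severity, and does not say that severe malaria should go without quinine. It is also true that silence about stopping primaquine is not an instruction to give both. These points limit the size of the hazard, which the documents do not establish. They do not supply the missing direction to staff.

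A reader might infer three stronger points, none of which the documents support:

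- **That the problem extends across the two-year follow-up.** Section 3.3.3 says that for persistent gametocytaemia "the patient can be treated with a single dose of Primaquine (0.75mg/kg", and the 28-day limit in Annex C belongs to a different list, "ANTIBIOTICS WITH ANTIMALARIAL EFFECT (Avoid during 28-day follow-up". But the single dose is optional and restricted to persistent gametocytaemia, and severe malaria would have to coincide with it. Counting monthly visits or comparing dose sizes would suggest a scale for which there is no evidence. Stopping primaquine would also achieve nothing once a single dose has been swallowed.
- **That Annex C is out of sight because the visible text never refers to it.** The numbered annexes and forms are not all shown, and a missing cross-reference is editorial in any case.
- **That the Day 28 result is affected, so that a reclassification rule is needed.** Section 3.2.5 already classifies these patients as failures.

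**Conclusion.** The inconsistency is real and minor. A member of staff who follows section 3.2.4 on any of the ten primaquine days could give a drug that Annex C says to avoid. Few patients should be affected, because severe malaria is excluded at entry. The protocol gives no rate of severe signs and no expected split between quinine and artesunate, so no number of patients can be put on it. No endpoint and no sample size is affected.

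The conclusion rests on two assumptions: that the Annex C list applies to antimalarials given as rescue, since it states no exception, and that the unseen national guidelines do not already direct staff to artesunate during primaquine. If they do, the amendment only makes that explicit. This is a cheap improvement, not a flaw in the design.

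**What to change.** Amend the first bullet of section 3.2.4 by adding: *In a patient receiving primaquine (Days 0-9), give IV artesunate; use parenteral quinine only if artesunate is not available, and then stop primaquine (see Annex C).* Outside those days the existing choice can stay. Quinine remains available as a fallback, so no patient with severe malaria goes untreated.

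The cost is one amended bullet, with no extra patients, visits or form fields. The downside is that a rare patient given quinine would not complete primaquine, so any later recurrence in that patient would follow a shortened course. Section 3.3.3 already has the total tablets of each drug recorded on Annex 7, so such a patient can be identified at analysis. No change to the outcome classification is needed.
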